### Interventions

Following baseline assessments (by the blinded assessor), participants will be randomised (as described above) to one of two groups;

1. Conventional vestibular rehabilitation

2. Virtual reality vestibular rehabilitation

Based on best available evidence [5,6] 6 treatments will be provided over an 8 week timeframe. Treatment will only be provided by physiotherapists who are at senior level and have experience in vestibular rehabilitation and all treating physiotherapists will attend periodic protocol training sessions. On their first attendance participants will undergo a standardised physiotherapy assessment which will elucidate their main problems. The interventions for both groups have been developed and will be based on six identified core elements of vestibular rehabilitation used in current clinical practice- education, relaxation, adaptation exercises, habituation exercises, balance and gait retraining and re-conditioning [33]. Programs are customised to symptoms and impairments, and are progressive. All participants will be asked to perform a home exercise program daily for 30-40 minutes. Each participant will receive a standardised weekly booklet detailing their exercises and containing an adherence diary. They will return the booklets at each treatment session and receive a new one. The booklets have been designed to look similar. Each is tripartite containing adaptation exercises, balance exercises and a walking program. The booklets, provided to both groups differ only in the balance exercises, the conventional group receiving conventional balance exercises [2,34] and the NWFP group receiving exercises developed in pilot work [20]. The NWFP records type, duration and frequency of exercises and this will be used as an additional record in the NWFP group.

Participants in the virtual reality group will be instructed in the use of the NWFP^® ^and will be given one on loan for use at home. Participants in the conventional group will be provided with a standard therapeutic foam balance mat (Sissel Balance Fit Pad). All patients will be reviewed a minimum of 4 times over 8 weeks for re-assessment, progression of exercises and advice by the treating therapist.

### Safety considerations

To address the risk of falling, participants will be provided with the necessary written and verbal instructions to prevent a fall (e.g. support nearby). Any adverse events will be reported to the participants consultant physician and an adverse event form filled out. Participants experiencing adverse events will be followed up and assessed by their treating physiotherapist and physician.

#### Data analysis

Data will be coded and entered in Microsoft Excel and statistical analysis will be performed using PASW 18 (SPSS Inc. Chicago) and Stata Statistical Software (Release 11, StataCorp LP, TX:). Intention to treat analysis and per protocol analyses will be performed [34]. Baseline data will be examined for comparability. Where there are missing data, the last observation will be carried forward. Data will be summarised using means, standard deviations and 95% confidence intervals for continuous variables, median and interquartile ranges for non-normal continuous or ordinal data and percentages for categorical data. Per-protocol analyses will be performed excluding patients with major deviations from the treatment protocol (defined as less than 50% adherence with treatment). Data will be examined for normality and t-tests used for data with two time points. A mixed ANOVA model will be used for data with three time points with the factors of group (NWFP or Conventional Group) and time (baseline, 8 weeks, six months). Within and between group differences and interaction effects will be calculated and post hoc analyses performed where indicated. Comparison of outcome measures between groups will be performed controlling of the baseline distribution of known predictor variables and the results will be reported as differences in means/medians and their confidence intervals [32,35]. The non-parametric equivalent will be used where data are not normally distributed or are non-parametric. A significance level of p < 0.05 will be set. Effect sizes for within and between groups comparison will also be calculated.

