### Outcome measures

Consenting participants will complete baseline assessments prior to randomisation. They will be retested post treatment (at 8 weeks). The primary endpoint is gait velocity (m/sec) at 8 weeks post baseline.

Gait velocity will be assessed using three dimensional gait analysis (3DGA) in the Royal College of Surgeons in Ireland, School of Physiotherapy's Movement Laboratory. The laboratory has a Vicon 250 motion analysis system (Vicon Motion Systems Ltd., Oxford, UK) and a Kistler force plate (Kistler Instruments Ltd., Winterthur, Switzerland). Vicon consists of five infra red cameras that are able to localize reflective markers (placed on the participant) in a three-dimensional coordinate system within 1.5 mm error. Because of its high level of accuracy and reliability, it is considered a "gold standard" for motion analysis. The Kistler force plate, in synchronicity with the Vicon is able to compute kinetic forces during gait as well as centre of mass and centre of pressure. Gait velocity will be recorded during four conditions; self selected speed eyes open, self selected speed eyes closed (towards a target), cadence of 120 steps per minute eyes open (paced with a metronome), and walking with head turns.

Secondary gait variables will also be investigated; percentage of a gait cycle spent in double support, base of support width (cm), centre of mass/centre of pressure moment arm (mediolateral) and centre of mass velocity and displacement. These variables have been identified by Krebs et al (2003) [8] as the most significant discriminators of success following vestibular rehabilitation The Dynamic Gait Index (DGI)[23] will also be assessed.

Other secondary outcomes will be;

1. Computerised dynamic posturography (Equitest-NeuroCom) [24]. This measures postural sway during six sensory conditions and returns sensory ratios that can be compared to normative data. The sensory organisation test (SOT) will be performed according to the protocol published by Equitest (Neurocom).

2. The Vestibular Rehabilitation Benefits Questionnaire (VRBQ) [25,26] and the Activities Specific Balance Confidence Scale (ABC) [27]. These are validated and reliable questionnaires for assessment of the effects of dizziness. Scores range from 0-100.

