3. Dynamic Visual Acuity (DVA) [28]. This will be measured using a computerised DVA test (Micromedical Technologies, Chatham, Illinois). The difference between static and dynamic visual acuity (at three head speeds) in LogMAR units will be measured using the protocol published by Micromedical Technologies.

4. The Hospital Anxiety and Depression Scale (HAD) [29]. This validated scale has been used previously in studies in vestibular rehabilitation and assesses non-somatic symptoms of anxiety and depression. Scores range between 0 and 21, scores between 8 and 10 are considered borderline and those above ten indicate clinical depression or anxiety.

5. Usability of virtual reality technology will be measured by the System Usability Questionnaire [21]. This is a 10 item questionnaire using Likert scales. Adherence will be recorded in the exercise booklets (and where allocated, on the NWFP) and satisfaction with treatment will be measured with a questionnaire developed by the researchers.

A six month follow up will be carried out. This will be confined to the primary outcome measure of gait velocity (m/sec), and secondary outcomes of computerised posturography, the VRBQ, ABC and DGI. Outcome measurement at each time point is shown in Table 1.

**Table 1 T1:** Time frame and outcome measures in the study

Outcome Measure	Baseline Assessment	Post treatment (8 weeks)	Post Treatment (6 months)
Gait Speed	**✓**	**✓**	**✓**
Dynamic Gait Index	**✓**	**✓**	**✓**
Dynamic Posturography	**✓**	**✓**	**✓**
Activities Balance Confidence Questionnaire	**✓**	**✓**	**✓**
Vestibular Rehabilitation Benefits Questionnaire	**✓**	**✓**	**✓**
Dynamic Visual Acuity	**✓**	**✓**	
Hospital Anxiety and Depression Scale	**✓**	**✓**	
Adherence/Satisfaction with treatment			
*Three Dimensional Gait Analysis*			
Centre of mass velocity and excursion	**✓**	**✓**	
Centre of mass/centre of pressure moment arm	**✓**	**✓**	
% gait cycle in double support	**✓**	**✓**	
step width (cm)	**✓**	**✓**	

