### Sample size and power calculation

Based on previously published work the estimated sample sizes for each outcome variable have been calculated (Table 2). The calculations were performed to detect what would be a clinically important difference between the means, with a significance level of 0.05 using the power calculation by Pocock [30] given as;

**Table 2 T2:** Sample size and power calculations for the trial

Outcome Measure	Mean Change Expected	SD	Sample Size Required (per group)
Gait Velocity (m/sec)	0.1	0.15	36
Vestibular Rehabilitation Benefit	-7	10.1	33
Questionnaire (%) [25]			
Static Posturography (% composite score)[31]	10	15	36
Dynamic Visual Acuity (LogMAR) [32]	0.1	.136	30

$$\text{n}=\frac{2\sigma^{2}}{{\left(\mu_{2}-\mu_{1}\right)}^{2}}\times \text{f}(\alpha ,\beta )$$

Where σ is the standard deviation, μ is the mean difference expected between the two groups using a two sample t-test, α is the significance level (P < 0.05) and β is the lower (0.80) and f (α,β) is 7.9. Allowing for a 5% drop-out rate a minimum of 37 patients will be required pergroup. Current referral rates of patients with unilateral vestibular loss to physiotherapy approximate 40-50 participants per year over the two sites, thus a two year recruitment period is required.

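### Last observation carried forward is the only missing-data rule; at 8 weeks it gives each missing participant zero change in gait velocity, which biases the primary comparison

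*Protocol article*

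**What the plan says.** The Data analysis section states: "Where there are missing data, the last observation will be carried forward". It is given for missing data generally, with no outcome exempted. No other missing-data method and no missing-data sensitivity analysis is named. The per-protocol analysis in the same section excludes participants with low adherence, which is a different matter.

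Under Outcome measures, "The primary endpoint is gait velocity (m/sec) at 8 weeks post baseline". Baseline assessment precedes randomisation, and the next assessment is the 8-week one. For later follow-up, "A six month follow up will be carried out", and it includes gait velocity. Table 1 lists gait speed at these three times only.

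Data analysis gives t-tests to outcomes with two time points and a mixed ANOVA (group by time) to outcomes with three, so gait speed falls under the mixed ANOVA. The section also plans comparisons that control for baseline predictors. The Sample size section plans "Allowing for a 5% drop-out rate".

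**The concern.** Nothing is measured between baseline and 8 weeks, so for the primary endpoint carrying the last observation forward means carrying baseline forward. Each participant without an 8-week value enters the intention-to-treat analysis with a change of exactly zero. This applies even to someone who misses week 8 but attends at 6 months. A missing 6-month value is frozen at the 8-week value, or at baseline if that is missing too, and the filled-in values feed the mixed ANOVA.

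Both arms receive active rehabilitation, which the article describes as effective. If participants gain on average, zero change understates what those with missing data would have shown, and the error in the treatment difference depends on how many are missing in each arm. Participants and therapists know the allocation, so equal retention cannot be taken for granted. At stake are a diluted effect in a superiority trial or, with unequal dropout, a difference produced by retention rather than by treatment.

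**Working it through.** **Inputs from the article.** Target difference 0.1 m/s, SD 0.15 and 36 per group (Table 2); significance level 0.05 and "f (α,β) is 7.9"; 5% dropout; 80 randomised (Abstract).

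**Assumed, because the article does not give them.** 40 per arm; correlation 0.7 between baseline and 8 weeks; the mean gain in each arm; dropout other than 5%; dropout unrelated to outcome.

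**The plan's own figure.** n = 2 × 0.15² / 0.1² × 7.9 = 35.55, so 36 per group, as stated.

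**Expected difference under the rule.** Let d be the share missing at 8 weeks and gain the mean change from baseline (N = NWFP, C = conventional). Missing participants contribute zero change, so:

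expected difference = (1 − dN) × gainN − (1 − dC) × gainC

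bias = −dN × gainN + dC × gainC

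**Equal dropout, true difference 0.10 m/s.** The expected difference is (1 − d) × 0.10, whatever the conventional-arm gain. Power does depend on that gain, assumed here to be 0.15 m/s. It was simulated with 4,000 runs per scenario, comparing the carried-forward analysis with the observed-data analysis under the same model.

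| Missing per arm | Expected difference (m/s) | t-test: carried forward / observed | Baseline-adjusted: carried forward / observed |
|---|---|---|---|
| 5% | 0.095 | 77% / 82% | 95% / 98% |
| 10% | 0.090 | 69% / 80% | 90% / 97% |
| 20% | 0.080 | 54% / 73% | 77% / 95% |

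The losses in this table are 5, 11 and 19 points for the t-test and 3, 7 and 18 for the baseline-adjusted analysis. Repeat runs shift them by one to three points; one put the t-test loss at 20% missing at 74 − 53 = 21.

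**Unequal dropout, true difference 0.10 m/s, conventional gain 0.10 m/s.**
- 20% NWFP, 5% conventional: 0.80 × 0.20 − 0.95 × 0.10 = 0.065.
- 5% NWFP, 20% conventional: 0.95 × 0.20 − 0.80 × 0.10 = 0.110.

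**No true difference, 5% NWFP and 20% conventional.** The bias is (0.20 − 0.05) × gain.

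| Gain in both arms (m/s) | Spurious difference (m/s) | Type I error, t-test to baseline-adjusted |
|---|---|---|
| 0.05 | 0.0075 | about 6% |
| 0.10 | 0.015 | about 7–10% |
| 0.15 | 0.0225 | about 9–14% |

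Reversing the dropout rates reverses the sign. The observed-data analyses stay near zero difference and 5% rejection.

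**Standard error.** With 20% missing in both arms, a gain of 0.10 m/s and no true difference, the baseline-adjusted standard error is 0.0237 under the rule and 0.0270 from observed data. The sampling spread of the carried-forward estimate is also 0.0237.

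**Limit of the check.** The simulations compare the arms at 8 weeks by t-test or baseline adjustment. They do not reproduce the planned mixed ANOVA, so the power and type I figures are a guide. The expected-difference formula holds for the between-arm difference in change to 8 weeks under any of these models.

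**The case against.** The strongest reply is that, at the dropout the article plans for, little happens. With 5% missing in each arm the bias is 0.005 m/s, one twentieth of the target, and type I error stays at about 5%. That stands. The larger figures rest on assumed dropout and assumed gains. The article gives no conventional-arm gain and calls the evidence for improvement in balance and gait less convincing, so 0.15 m/s may be generous.

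Zero change may also be less far-fetched than it looks. A reader might infer from the Background that these patients would recover anyway through vestibular compensation. The article does not support this: it describes that recovery for most patients in the acute phase, whereas the inclusion criteria require complaints that indicate failed compensation. Someone who leaves treatment early may change little. This argues for testing the assumption in a sensitivity analysis, not for imposing it on everyone with missing data.

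Two further inferences go too far. One is that the standard errors are simply wrong. Under random dropout the standard error matches the spread of the carried-forward estimate; what remains is that imputation uncertainty is ignored and the interval is centred on a biased value. The other is to set 69% or 54% power under the rule against 95–97% for a baseline-adjusted observed-data analysis. That changes two things at once: with no dropout at all, the t-test has 84% power and the baseline-adjusted analysis 98%. Moreover, the article does not assign gait speed to a t-test.

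**Conclusion.** The flaw is real and should be fixed, but the plan does not stand or fall on it. That a missing 8-week value becomes zero change follows from the stated rule and the visit schedule. The bias formula assumes only that those with missing data would on average have gained as much as the rest of their arm.

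The size depends on retention. With equal dropout a true 0.10 m/s shrinks by the dropout proportion, and under the assumptions above the like-for-like power loss is about 3 to 5, 6 to 11 and 18 to 21 points at 5%, 10% and 20%. With strongly unequal dropout and a sizeable gain in both arms, the false-positive rate can double or more. A reader might conclude that the primary result is already compromised at the planned dropout; the article's own 5%, if equal in the arms, does not support that. The statistical analysis plan is not shown and may refine the rule, but the article states this one without qualification.

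**What to change.** Replace the carried-forward sentence with wording such as: *Gait velocity will be analysed with a likelihood-based linear mixed model of all observed values, adjusted for baseline; missing values will not be singly imputed. A sensitivity analysis will use multiple imputation with a range of shifts, set separately by arm, that make missing outcomes worse than missing at random implies.*

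Baseline-adjusted ANCOVA at 8 weeks with multiple imputation would serve equally well. The mixed model has the advantage of using the 6-month value of a participant who missed week 8. The same rule should replace the carried-forward values in the three-time-point analyses.

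The change should be made before unblinded data are seen. Sample size, visits and participant burden stay as they are. The cost is a revised analysis paragraph and slightly more programming for the sensitivity analysis.

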**Figure 2 F2:**
[figure not shown]
**CONSORT (2010) flow diagram of the trial**.

Study objectives

1. To compare the effect of conventional vestibular rehabilitation and virtual reality based rehabilitation on gait impairment.

2. To compare the effect of conventional vestibular rehabilitation and virtual reality based rehabilitation on balance.

3. To compare the effect of conventional vestibular rehabilitation and virtual reality based rehabilitation on dizziness and vertigo.

4. To compare the effect of conventional vestibular rehabilitation and virtual reality based vestibular rehabilitation on dynamic visual acuity.

5. To quantify and compare patient satisfaction and adherence with conventional and virtual reality based vestibular rehabilitation.

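### Secondary outcomes measured only at baseline and 8 weeks go to an unspecified t-test, where ANCOVA on the outcome's own baseline would be more precise at almost no cost

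*Protocol article*

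**What the plan says.** The Data analysis section splits outcomes by number of time points. For two, "Data will be examined for normality and t-tests used for data with two time points". For three, "A mixed ANOVA model will be used for data with three time points with the factors of group (NWFP or Conventional Group) and time". The same section later adds: "Comparison of outcome measures between groups will be performed controlling of the baseline distribution of known predictor variables". It also sends non-normal data to a non-parametric equivalent.

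The Outcome measures section and Table 1 show which outcomes fall under the two-time-point rule. Six-month follow-up is confined to gait velocity and the "secondary outcomes of computerised posturography, the VRBQ, ABC and DGI". That leaves baseline and 8 weeks only for DVA, HAD, percentage of the cycle in double support, step width, the centre of mass/centre of pressure moment arm, and centre-of-mass velocity and excursion. Their baseline values will exist for every randomised patient: "Consenting participants will complete baseline assessments prior to randomisation".

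DVA is defined as a difference score: "The difference between static and dynamic visual acuity (at three head speeds) in LogMAR units will be measured". It is the subject of objective 4, "To compare the effect of conventional vestibular rehabilitation and virtual reality based vestibular rehabilitation on dynamic visual acuity", and is the only two-time-point outcome sized in Table 2, whose effect column is headed "Mean Change Expected".

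**The concern.** The rule names a test without saying what it is applied to. There are three possible readings:

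- A two-sample t-test on 8-week values sets the baseline measurement aside.
- A two-sample t-test on change uses the baseline, but with its slope fixed at 1.
- A paired t-test within each arm does not compare the arms at all.

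The later sentence on controlling for baseline predictors does not settle the matter. It names no model and does not say that the outcome's own baseline is one of the predictors. A plain t-test takes no covariate. An analyst could therefore report an unadjusted or an adjusted result for the same outcome and cite the protocol for either.

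What is at stake is precision, and sensitivity to chance baseline differences, in a trial of about 40 patients per arm.

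**Working it through.** **Inputs.** From Table 2 for DVA: difference 0.1 LogMAR, SD 0.136, 30 per group. From the sample-size text: significance level 0.05 and multiplier f = 7.9, which corresponds to 80% power with a two-sided test. The abstract plans 80 patients, so 40 per arm if split equally; 5% drop-out leaves 40 × 0.95 = 38. The figure of 36 per group is the largest in Table 2. The correlation r between baseline and 8-week values is not given; 0.5 is assumed, with 0.3 to 0.7 as the range.

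**The plan's own figure.** n = 2 × 0.136² / 0.1² × 7.9 = 29.2, rounded up to 30. Table 2 reproduces.

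**Variance of the estimated group difference.** Take equal SDs at baseline and 8 weeks, and set the t-test on 8-week values to 1:

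- t-test on 8-week values: 1
- t-test on change: 2(1 − r)
- ANCOVA: 1 − r²

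ANCOVA relative to the first is 1 − r². Relative to the second it is (1 − r²) / [2(1 − r)] = (1 + r)/2. Both ratios are below 1 for every r strictly between 0 and 1.

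| r | ANCOVA vs 8-week values | ANCOVA vs change |
|---|---|---|
| 0.3 | 0.91 | 0.65 |
| 0.5 | 0.75 | 0.75 |
| 0.7 | 0.51 | 0.85 |
| 0.8 | 0.36 | 0.90 |

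**Chance baseline imbalance.** A difference of 1 unit between arms at baseline leaves r units in a comparison of 8-week values, −(1 − r) units in a comparison of change, and 0 in ANCOVA. At r = 0.3 that is 0.3 and −0.7; at r = 0.7 it is 0.7 and −0.3. The two t-tests err in opposite directions.

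**Power for DVA** (noncentral t, standardised difference 0.1 / 0.136 = 0.735). For ANCOVA the SD is multiplied by √(1 − r²) if 0.136 is the SD of final values, or by √((1 + r)/2) if it is the SD of change. At r = 0.5 both variance factors are 0.75:

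| Per group | t-test | ANCOVA, r = 0.5 | Gain (points) |
|---|---|---|---|
| 30 | 80.0% | 89.9% | +9.9 |
| 36 | 86.8% | 94.4% | +7.6 |
| 38 | 88.6% | 95.5% | +6.9 |

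Range at 36 per group, against 86.8%:

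| r | SD is of final values | SD is of change |
|---|---|---|
| 0.3 | 89.7% (+2.9) | 96.8% (+10.0) |
| 0.7 | 99.1% (+12.3) | 91.6% (+4.8) |

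Spending one extra degree of freedom on the covariate changes these figures by less than 0.1 point. At r = 0.5 the confidence interval narrows by 1 − √0.75 = 13%.

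**The case against.** A reader might infer that baseline is ignored altogether. The document does not support that. A t-test on change uses baseline, the wording about two time points fits a change score at least as well as a comparison of 8-week values alone, and the effect column of Table 2 is labelled as change. On that reading the complaint is about efficiency only, and the gain shrinks as r rises: at r = 0.8 the variance falls by just 10%.

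The section also promises baseline-controlled comparisons for outcome measures in general. These may be separate from the t-tests, and an outcome's own baseline is an obvious candidate predictor. This objection stands in part: the plan may intend the right adjustment, but it does not say so and does not say which result is the one to report.

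A reader might also infer that the t-test is biased or the trial underpowered. Neither follows. Under randomisation both two-sample t-tests are valid; an imbalance matters conditionally, once it has occurred. DVA exceeds 80% power with the plain t-test. The primary outcome, gait velocity, has three time points and is analysed by the mixed ANOVA, so this point does not touch it.

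Two limits stand. HAD and the gait variables under this rule have no effect or SD in the document, so the gain for them cannot be quantified. HAD, a bounded score from 0 to 21, may be sent to a non-parametric test and never reach a t-test.

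The objection that such detail belongs in an analysis plan does not dispose of the point. The article names a test, and a better one is available with data already scheduled.

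**Conclusion.** The point holds as a recommended improvement for secondary outcomes. The plan fixes an under-specified t-test where baseline-adjusted ANCOVA has lower variance than either between-group version for any r strictly between 0 and 1, and it leaves unclear how that t-test relates to the promised controlled comparison. For DVA at 36 per group the gain is 7.6 points of power at r = 0.5. It lies between 2.9 and 12.3 points over r from 0.3 to 0.7, depending also on whether the Table 2 SD is of final values or of change.

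These sizes rest on an assumed r, equal SDs at both visits, and the Table 2 inputs. No conclusion about the primary outcome depends on them.

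**What to change.** In the Data analysis section, replace the two-time-point t-test rule with wording to this effect:

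> For outcomes measured at baseline and 8 weeks only, the between-group difference at 8 weeks will be estimated by a linear model with treatment group and the baseline value of that outcome as covariate, and reported with its 95% confidence interval. This is the baseline-controlled comparison for these outcomes. T-tests will be descriptive only. Where a score is clearly non-normal (for example HAD), a rank-based or bootstrap version of the same baseline-adjusted comparison will be used.

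The last part is needed so that the change agrees with the section's existing non-parametric rule.

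The cost is a short edit to one section and one degree of freedom per outcome. No visits, measurements or patients are added, because Table 1 already schedules every baseline value, and the two packages named in the plan can fit the model.

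### The rule that sends gait velocity to a three-visit mixed ANOVA leaves the 8-week group difference, the endpoint the trial was sized for, without a designated primary test

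*Protocol article*

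**What the plan says.** Outcome measures fixes both the endpoint and its time: "The primary endpoint is gait velocity (m/sec) at 8 weeks post baseline". Sample size and power calculation sizes the trial on one "mean difference expected between the two groups using a two sample t-test", with 0.1 m/sec, SD 0.15 and 36 per group in Table 2.

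The 6-month follow-up also covers gait velocity ("This will be confined to the primary outcome measure of gait velocity (m/sec"), and Table 1 marks it at all three visits.

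Data analysis then chooses the method by the number of visits. The simple test is reserved for the shorter series: "t-tests used for data with two time points". For the rest, "A mixed ANOVA model will be used for data with three time points with the factors of group (NWFP or Conventional Group) and time", the levels being "time (baseline, 8 weeks, six months". The next sentence reads "Within and between group differences and interaction effects will be calculated and post hoc analyses performed where indicated". A further sentence promises a between-group comparison that controls for baseline predictors, reported with confidence intervals. It does not list the predictors or give a visit.

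**The concern.** Read together, these sections take the primary outcome out of the test used to size the trial and put it into a model whose headline tests answer other questions. The group main effect asks whether the arms differ on average over three visits, one of which is before treatment. The interaction asks whether the arms have different profiles over time, at any visit. The primary endpoint asks whether they differ at 8 weeks.

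The main effect, the interaction, a post hoc contrast and the adjusted comparison can disagree, and the article does not say which one decides the trial. A difference seen only at 6 months could then be reported as a positive group-by-time result when there is no effect on the stated primary endpoint.

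In addition, baseline velocity enters the stated model as a response level. It is not named as a covariate, although it is collected for every participant.

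**Working it through.** **Inputs from the article.** Difference 0.1 m/sec, SD 0.15, 36 per group, significance level 0.05, f = 7.9.

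**Assumptions not in the article.** Equal between-visit correlation ρ (0.3 to 0.8), the same SD at each visit, equal baseline means, two-sided testing. Table 2 does not settle whether 0.15 is the SD at one visit or the SD of change, so both readings are shown.

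**1. The plan's own figure.** 2 × 0.15² / 0.1² × 7.9 = 35.55, rounded up to 36. It reproduces. Exact power of the 8-week t-test at 36 per group is 79.7%.

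**2. Group main effect (0.15 per visit).** The tested difference is (0 + 0.1 + d₆)/3, where d₆ is the 6-month difference. The SD of a participant's three-visit mean is 0.15 × √((1 + 2ρ)/3). With a sustained effect and ρ = 0.5, the difference is 0.067 and the SD 0.122.

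**3. Interaction (0.15 per visit).** The noncentrality is λ = (36/2) × Σ(d_t − d̄)² / (0.15² × (1 − ρ)), referred to F with 2 and 140 df. For a sustained effect the sum of squares is 0.00667, so λ = 10.7 at ρ = 0.5. For an effect halved at 6 months it is 0.005, so λ = 8.0.

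| 6-month effect | Test | ρ = 0.3 | 0.5 | 0.7 | 0.8 |
|---|---|---|---|---|---|
| sustained (0.1) | main effect | 72.1% | 62.5% | 54.7% | 51.5% |
| | interaction | 68.5% | 83.3% | 97.0% | 99.7% |
| halved (0.05) | main effect | 48.0% | 40.1% | 34.5% | 32.2% |
| | interaction | 55.2% | 70.8% | 90.9% | 98.3% |
| gone (0) | main effect | 24.7% | 20.7% | 18.0% | 17.0% |
| | interaction | 68.5% | 83.3% | 97.0% | 99.7% |

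**4. Nothing at 8 weeks, 0.1 at 6 months only.** The sum of squares is again 0.00667, so the interaction is significant 83.3% of the time at ρ = 0.5 and 97.0% at ρ = 0.7. These are the same figures as for an effect present at 8 weeks only. The interaction p-value cannot tell the two cases apart.

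**5. The 8-week contrast adjusted for baseline.** The residual SD is 0.15 × √(1 − ρ²) on the per-visit reading and 0.15 × √((1 + ρ)/2) on the change reading, with 69 df.

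| Reading of 0.15 | ρ = 0.3 | 0.5 | 0.7 | 0.8 | Unadjusted reference |
|---|---|---|---|---|---|
| SD at a visit | 83% | 90% | 97% | >99% | 80% (t-test at 8 weeks) |
| SD of change | 93% | 90% | 86% | 84% | 80% (t-test on change) |

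On the change reading the interaction has 83% power if the effect is sustained or gone and 71% if it is halved, at every ρ.

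**The case against.** Four objections deserve an answer.

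- **The 8-week comparison is not excluded.** A reader might infer that it survives only as a conditional follow-up test, from "post hoc analyses performed where indicated". The sentence does not support that. The condition attaches to the post hoc analyses, while between-group differences are promised without condition, as is the adjusted comparison in the later sentence. An 8-week difference could come from either. What remains is that neither is tied to 8 weeks or named as the deciding test.
- **The interaction is the usual treatment test in this design and is not generally weak.** This stands. On the per-visit reading with ρ from 0.5 to 0.8, it falls below 80% only at ρ = 0.5 with a halved 6-month effect. At ρ = 0.7 with a sustained effect it matches the adjusted 8-week analysis (97% each). With the 80 patients planned, taken as 40 per group, its lowest value in that range is 76%.
- **Baseline is not ignored.** This also stands in part. The interaction compares changes over time, and baseline velocity could be among the unlisted predictors. The article does not say so, and it does not explain how a level of the time factor would also be a covariate.
- **A condensed article leaves covariates and contrasts to the full plan.** That would answer a mere gap. Here the article itself selects the model by number of visits, and that rule does not match its own endpoint and sample size.

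**Conclusion.** The concern holds as a mismatch of target. The stated rule gives the primary outcome a model in which neither omnibus test is the 8-week contrast, and no analysis is designated as primary. The clearest measure is the 83% to 97% chance, at ρ of 0.5 to 0.7 and 0.15 per visit, that a 6-month-only difference of 0.1 m/sec makes the interaction significant.

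It does not hold as a general claim of lost power. The loss is plain for the main effect (about 17% to 62% at ρ of 0.5 to 0.8, per-visit reading). For the interaction it depends on ρ, on the course of the effect after 8 weeks and on which SD 0.15 is.

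A reader might also infer that t-tests are wrong for the outcomes measured at two visits. They are valid under randomisation; adjusting each for its own baseline is an optional gain in efficiency.

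All power figures rest on an assumed ρ and on equal correlation between visits. The mismatch itself rests on the text alone.

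**What to change.** Replace the rule for gait velocity in Data analysis with a sentence such as: *The primary analysis is the between-group difference in gait velocity at 8 weeks, adjusted for baseline gait velocity, estimated with a 95% confidence interval and tested at two-sided 0.05.* This can be an ANCOVA. It can equally be a repeated-measures model with the 8-week and 6-month values as outcomes, baseline velocity as covariate, group-by-visit terms and the 8-week contrast prespecified.

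Label the 6-month contrast as secondary, and say which baseline predictors the adjusted comparison uses. It would also help to state in Table 2 whether 0.15 is the SD at a visit or of change.

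The cost is a few sentences. No extra patients, visits or measurements are needed, and the sample size of 36 per group before drop-out can stay.
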